### Interim analyses {21b}

No interim analysis will be performed because there are no anticipated problems that are detrimental to the participants.

### Methods for additional analyses (e.g. subgroup analyses) {20b}

There is no intention to perform additional analyses.

### Methods in analysis to handle protocol non-adherence and any statistical methods to handle missing data {20c}

If children and families drop out from treatment, we will try to continue measurements according to the randomized treatment condition and analyses will primarily be performed according to the principles of intention-to-treat. This means families are analyzed as participants of the treatment condition they are randomized to. However, analyses will be repeated as per-protocol analyses, which means that families are analysed as participants of the condition they actually received.

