#### Effectiveness study of FITT

This study examines to which extent FITT is an effective treatment for concurrent reduction of children’s trauma symptoms, improvement of parenting functioning, and enhanced emotional and physical security in children, through the improvement of parent-child relationships—in order to establish long-term effects on the reduction of trauma symptoms and recovery of security in the family. In this multi-centre study with a randomized controlled design, we compare FITT with an intensive trauma treatment without a parent and systemic component (ITT) and with treatment as usual (TAU) and low-frequency trauma treatment with parent therapy and family sessions). Comparing these interventions with and without specific components contributes to understanding if these interventions are effective and how these interventions work [49]. These insights may be used to increase treatment effectiveness [50] for adolescence with complex traumatic experiences. To further detect the mechanism of change, we included measurements during treatment [50].

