#### Sample size {14}

Power analysis was conducted to determine whether an informative trial could be conducted given limitations imposed upon the maximum sample due to the duration of the study and size of the population of children indicated for trauma treatment, using G*power 3 [95]. Sample size calculation was made based on the assumptions of the primary objective and the first secondary objective. A priori, we decided that adding systemic intervention elements to individual trauma therapy would be justified if it would mean that on average at least one out of five children would have clinically significant benefit when given the full FITT compared to treatment without systemic elements (number needed to treat = 5; equivalent to *f* = 0.18).

For primary objective 1 (Does intensive trauma therapy with a family-based component (FITT) lead to a stronger reduction of trauma symptoms and stronger increase of structural emotional safety than intensive trauma therapy without this family-based component (ITT)?), the sample size was calculated based on between 2 groups by within effect with at least two measurements (pre, end/follow-up), setting *f* = 0.18 with a power of 80% and a significance level of 5% (two-sided). Default settings were used for the correlation among repeated measures (= 0.5) and non-sphericity correction (*ε* = 1). According to the power analysis, a total sample size of 64 children is required.

Secondary objective 1 (Does intensive trauma therapy with a family-based component (FITT) lead to faster reduction of trauma symptoms and increase of structural emotional safety than low-frequency trauma treatment with parent therapy and family sessions?) is based on two measurements (pre and intermediate/follow-up). In accordance with the first sample size calculation, we tested with setting *f* = 0.18 with a power of 80%, a significance level of 5% (two-sided) was used. Again, default settings were used for correlation among repeated measures (= 0.5) and non-sphericity correction (*ε* = 1). Based on this calculation, a total sample size of 64 children is required.

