## Statistical methods

### Statistical methods for primary and secondary outcomes {20a}

The measurement level of each variable is at least ordinal. We control for the duration and severity of family violence [96], child functioning, parental psychopathology [97], and new incidents of family violence as a priori potential confounders. Analyses will be performed using the latest version of the software package Statistical Package for the Social Sciences (SPSS). First, to determine whether changes on continuous measures are different per treatment, we use linear mixed models. Continuous measures with only one time point will be analysed with independent samples *T*-test. Changes in categorical outcomes over the course of treatment across the conditions are tested with generalized estimating equations (GEE). To handle missing data, we will use maximum likelihood estimation within the linear mixed model analyses. For the planned GEE, we will explore the possibilities to deal with missing data, depending on the amount, randomness, and type of data missing. Analyses will primarily be performed according to the principles of intention-to-treat; however, they will be repeated as per-protocol analyses (see Table 4).

**Table 4 Tab4:** Statistical analyses

*Statistical analyses*					
	Measure	Type of data	Timepoints	Statistical analysis	Subjects
Child PTSD	CAPS-CA	Categorical	3	GEE	ITT/PP
	CRIES	Continuous	4	Mixed models	ITT/PP
	TSCC	Continuous	3	Mixed models	ITT/PP
Child functioning	SDQ	Continuous	3	Mixed models	ITT/PP
	CDI	Continuous	3	Mixed models	ITT/PP
	CDC	Continuous	3	Mixed models	ITT/PP
Parent functioning	NOSI-K	Continuous	4	Mixed models	ITT/PP
	Trauma-informed	Continuous	3	Mixed models	ITT/PP
	TSI	Continuous	3	Mixed models	ITT/PP
	YAS-R	Continuous	3	Mixed models	ITT/PP
	DPAS	Continuous	3	Mixed models	ITT/PP
Structural emotional and physical safety	CTS	Continuous	3	Mixed models	ITT/PP
	CTS-pc	Continuous	3	Mixed models	ITT/PP
	PRTI	Continuous	3	Mixed models	ITT/PP
	ACE-Q	Continuous	3	Mixed models	ITT/PP
	New IPV incidents	Continuous	4	Mixed models	ITT/PP
	SIS	Continuous	3	Mixed models	ITT/PP
	SIFS	Continuous	3	Mixed models	ITT/PP
	SIM-PR	Continuous	3	Mixed models	ITT/PP
	Security scales	Continuous	3	Mixed models	ITT/PP
	FIT	Categorical	1	Independent samples T-test	ITT/PP

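### The analysis labelled per-protocol groups families by treatment received, so it is an as-treated analysis and can bias the supportive FITT-ITT contrast in either direction

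*Protocol article*

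**What the plan says.** Under Statistical methods {20a}: "Analyses will primarily be performed according to the principles of intention-to-treat; however, they will be repeated as per-protocol analyses". The Subjects column of Table 4 lists both analysis sets for all 21 measures.

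The section on protocol non-adherence {20c} defines the two sets. On intention-to-treat: "This means families are analyzed as participants of the treatment condition they are randomized to". The repeat is then described as "per-protocol analyses, which means that families are analysed as participants of the condition they actually received".

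The arms are nested. Under Effectiveness study of FITT: "we compare FITT with an intensive trauma treatment without a parent and systemic component (ITT"). The intervention description adds to the ITT programme a psycho-education session shared with parents and network, parent therapy in weeks 2 and 3, and family therapy in week 4.

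The article does not say how much of a programme counts as having received it, or where a family that completes no condition is placed.

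**The concern.** A per-protocol analysis keeps families in their randomised arm and drops those who departed materially from the protocol. The rule in {20c} moves families between arms, which is a different analysis with a different bias.

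The distinction matters here because of the nesting. A FITT family that takes up none of the parent and family components has received essentially ITT content, and under the stated rule can be counted as ITT. The groups are then sorted by uptake of the very component under test. If uptake is related to prognosis, the FITT-ITT contrast in this repeat mixes the component's effect with the difference between families who engage and families who do not.

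The Discussion presents the pair of analyses partly as protection against selection bias; regrouping by treatment received can introduce it. Because no additional analyses are planned ({20b}), this repeat is the only alternative analysis set described, and readers will take its label at face value.

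**Working it through.** **1. The plan's own figure.** The Sample size section gives "number needed to treat = 5; equivalent to *f* = 0.18", two groups, two measurements, correlation 0.5, 80% power and 5% two-sided. For the group-by-time interaction, λ = f²·N·m/(1 − ρ) with 1 and N − 2 degrees of freedom. At N = 64, λ = 0.0324 × 64 × 2/0.5 = 8.29 and power is 0.809; at N = 62 it is 0.796. So 64 is the smallest even total that reaches 80%. Three arms of 32 give 96, and 96/0.80 = 120. Both stated figures reproduce, and the present point does not change them.

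**2. Effect implied by that model.** Difference in change = 2·√(f²·m/(1 − ρ)) = 2·√(0.0324 × 4) = 0.72 SD, that is, 4f. With ρ = 0.5 the SD of change equals the SD of a single measurement.

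**3. Bias from regrouping.** Two inputs are not in the article and are assumed: q, the share of families who would not take up the parent and family components if offered them, and g, how much worse (in SD) such families do whatever the arm. Set the overall mean to zero and assume no treatment effect. Takers then average +gq and non-takers −g(1 − q).

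- FITT as treated (takers only): gq.
- ITT as treated (all ITT families plus FITT non-takers): −qg(1 − q)/(1 + q).
- Difference: gq + qg(1 − q)/(1 + q) = **2qg/(1 + q)**.
- If FITT non-takers are excluded instead and the ITT arm is left whole: **qg**.
- Intention-to-treat: 0.

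| q | g (SD) | As-treated bias 2qg/(1 + q) | Exclusion bias qg |
|---|---|---|---|
| 0.1 | 0.3 | 0.06/1.1 = 0.055 | 0.03 |
| 0.1 | 0.5 | 0.10/1.1 = 0.091 | 0.05 |
| 0.2 | 0.3 | 0.12/1.2 = 0.100 | 0.06 |
| 0.2 | 0.5 | 0.20/1.2 = 0.167 | 0.10 |
| 0.3 | 0.5 | 0.30/1.3 = 0.231 | 0.15 |
| 0.2 | 0 | 0 | 0 |
| 0.2 | −0.5 | −0.20/1.2 = −0.167 | −0.10 |

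Positive values favour FITT. The figures are unadjusted for covariates.

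**4. Type I error.** Simulated with no true effect, 32 per arm, 10,000 runs, two-sided 5% t-test. The as-treated rejection rate was 0.049 (q = 0.2, g = 0), 0.091 (0.2, 0.5), 0.128 (0.3, 0.5) and 0.096 (0.2, −0.5). Intention-to-treat stayed between 0.049 and 0.051.

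**The case against.** The strongest reply is that this is a mislabelled supportive analysis and that the trial's main answer does not depend on it. That stands: intention-to-treat is primary and correctly defined.

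Four further points limit the concern.

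- **Direction.** A reader might infer that the rule biases the contrast toward FITT. The article gives neither a non-uptake rate nor a prognosis gap. Less engaged families may well do worse, but families who improve early could also skip the family sessions, and the sign would then reverse.
- **Who is moved.** A reader might infer that every non-adherent FITT family is reassigned, or that families could land in any arm. With no threshold for having received a condition, partial attenders could stay in FITT. Only a move to ITT follows from the nesting; counting as TAU would require receiving the low-frequency programme. Eligibility criterion (e), caregivers able to join the systemic components, makes complete non-uptake less likely.
- **Covariates.** {20a} already plans adjustment for violence severity and duration, child functioning, parental psychopathology and new incidents. This would remove the part of g that those variables explain. It cannot be relied on to remove all of it.
- **Benchmark.** A reader might set the bias against 0.36 SD, which is 2f and appears nowhere in the article. Against the 0.72 SD implied by the stated power model, the same bias is relatively half as large.

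Nor does the article say that the FITT-TAU equivalence conclusion at follow-up rests on this set. The most that can be said is that readers often look to a per-protocol set to corroborate equivalence, and here that label would mislead them.

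**Conclusion.** The definition in {20c} is wrong for its label and should be corrected. The analysis described is as-treated, it does not preserve the randomised groups, and it is repeated for all 21 measures. It can bias the supportive FITT-ITT contrast because FITT families who do not take up the added components can be counted as ITT.

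The size is conditional. At an assumed 10-30% non-uptake and a prognosis gap of 0.3-0.5 SD, the spurious difference is 0.055-0.23 SD in favour of FITT, about 8% to 32% of 0.72 SD (0.055/0.72 and 0.23/0.72). These figures assume that every non-taker is moved and that there is no covariate adjustment. The bias is zero when g = 0 and runs against FITT when g is negative.

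The mislabel is certain; the direction and size of the bias are not. The primary analysis and the sample size are unaffected.

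**What to change.** In {20c}, choose one of two routes.

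1. **Redefine per-protocol.** Analyse families in the arm to which they were randomised, and keep those who received a stated minimum of that arm's sessions. Fix the minimum for each arm before outcomes are seen. Families who complete no condition are excluded from this set. Take session receipt from the therapist evaluation forms described in {11c} where these allow. The article says the forms monitor adherence after each session but does not mention attendance, so check that they record it.
2. **Keep the present analysis under its proper name.** Call it as-treated, label it exploratory, and state what counts as having received each condition and where families who complete none are placed.

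Under either route, call the analysis supportive and draw no effectiveness or equivalence conclusion from grouping by treatment received. Retain the planned covariate adjustment. State that route 1 reduces selection bias without removing it: at 20% non-uptake and a 0.5 SD gap, about 0.10 SD remains, against 0.17 SD as-treated.

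The cost is one paragraph and a somewhat smaller sensitivity set. At 20% non-uptake, for example, about 26 of 32 FITT families would remain (0.8 × 32 = 25.6).

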### Plans to give access to the full protocol, participant level-data and statistical code {31c}

With this publication, public access to the full protocol is granted. Because of privacy regulation and data protection, the participant-level dataset is not accessible. Statistical code will be available upon request.

### Oversight and monitoring

#### Composition of the coordinating centre and trial steering committee {5d}

Daily monitoring of the study will be done by the coordinating investigator, project leader, and principal investigator. Frequent contacts with the four trauma centres and research team meetings will be held to evaluate the progress of the study. All participating trauma centres have a contact person, who will be involved in all phases of the research. Furthermore, an independent physician of each participating centre monitors the trial on-site and randomly check the research of participants. Participants can consult an independent expert with questions about the trial.

#### Composition of the data monitoring committee, its role and reporting structure {21a}

To monitor the collection, storage, and processing of the data, peer auditors trained in data management will randomly check the research file on the following:
Presence of informed consentsInclusion pace and drop out percentagePresence and completeness of the research data

If any errors are observed, the files of all study participants within the specific centre will be checked.

The presence and completeness of the research data will also be done on a daily basis by the research team.

#### Adverse event reporting and harms {22}

Adverse events are defined as any undesirable experience occurring to a subject during the study, whether or not considered related to the intervention. All adverse events reported spontaneously by the subject or observed by the investigator or the research team will be recorded. Should a child or a parent seem adversely affected by the questionnaires, interviews or observational task as observed by the researcher or therapist or as reported by the parents or children themselves, it may be decided to (temporarily) discontinue participation in the project. The investigator will report all SAEs to the sponsor without undue delay after obtaining knowledge of the events.

The sponsor will report the SAEs through the web portal *ToetsingOnline* to the accredited Medical Ethical Committee that approved the protocol, within 7 days of first knowledge for SAEs that result in death or are life-threatening followed by a period of a maximum of 8 days to complete the initial preliminary report. All other SAEs will be reported within a period of maximum 15 days after the sponsor has first knowledge of the serious adverse events.

All AEs will be followed until they have abated, or until a stable situation has been reached. Depending on the event, follow-up may require additional tests or medical procedures as indicated, and/or referral to the general physician or a medical specialist.

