#### Preparation phase: psycho-education and clustering

The preparation phase consists of two treatment days. On the first treatment day, the adolescent receives a 90-min online and interactive session of psycho-education about the impact of trauma and the treatment program. The aim is to inform the adolescent about (the consequences of) family violence, trauma and PTS disorder, stress regulation, the window of tolerance, and the treatment program. On the second treatment day, the adolescent is offered a 90-min session in which the different traumatic events are clustered. The adolescent and the therapist choose the six most traumatic memories, ordered by the degree to which they cause flashbacks, nightmares, and avoidance behaviour and elicit the most tension. These traumatic events will be the focus of the exposure and EMDR sessions.

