#### Intensive phase: exposure, EMDR, and bodily oriented therapy

In the intensive phase, the adolescent has three treatment days per week. Each treatment day has a fixed program consisting of the following:
90-min Exposure60-min bodily oriented therapy90-min EMDR

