##### Components of TAU

TAU is comparable across the four trauma centres and consists of low-frequent trauma-focused therapy with parenting therapy and family sessions. In contrast to the high intensity of FITT, TAU is offered about once a week and without therapist rotation. In TAU, the adolescents receive therapy from one therapist and parents receive therapy from another therapist. This individual or group-based trauma-focused cognitive behavioural therapy for adolescents and their parents is focused on the following components:
Psycho-education trauma and PTSD: increasing knowledge about (the consequences of) trauma and family violence and trauma-sensitive parenting and understanding the window of toleranceAffect regulation and coping: learning children to recognize and regulate feelings of stress and enhancing coping skillsTrauma processing: EMDR, exposure, writing therapy, or bodily oriented therapyParenting skills and competence: enhancing trauma-sensitive parenting skills, lowering levels of parental stress, and increasing social support.On indication: family relationships—sharing the trauma narrative and accompanying feelings and cognitions (for example feelings of shame or guilt) and strengthening of skills to prevent escalations

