#### Strategies to improve adherence to interventions {11c}

To increase treatment fidelity, a training protocol for (F)ITT is developed, and the therapists receive training in the (F)ITT protocol before data collection. Furthermore, therapists receive supervision on exposure, EMDR, parent and family therapy, and bodily oriented therapy during data collection. Exposure supervision is given by a healthcare psychologist who is a licensed supervisor from the Dutch cognitive-behavioural therapy association. EMDR supervision is given by healthcare and clinical psychologist who both are licensed supervisors from the Dutch EMDR association. The supervisor for the parent and family sessions is a clinical psychologist with advanced experience in the field of trauma and family therapy. The supervisor for the bodily oriented therapy is an experienced psychomotor therapist who works with traumatized children. To monitor adherence to the treatment protocol, therapists are asked to fill in a treatment evaluation form after each therapy session.

The trial will be monitored by the independent physician of the four participating youth mental health centres. Two times per year, the independent physician will randomly check the research file of a study participant on the following:
The involvement of a therapist registered in the Dutch register for healthcare professionalsThe presence of a safety plan in cases of suicidal thoughts/ideations and/or self-damaging behaviourThe compliance of in- and exclusion criteria (in the first year, the first three study participants will be checked, and thereafter, every half year, a participant will be randomly checked on in and exclusion criteria)Serious adverse events (SAEs) and if these are reported to the independent physician, inspection for healthcare and youth, the research institute and the Medical Ethical CommitteeThe presence of the cause conceptualisation

If any errors are observed, the files of all study participants within the specific centre will be checked.

To monitor the collection, storage, and processing of the data, each year, peer auditors trained in data management will randomly check the research file on the following:
Presence of informed consentsInclusion pace and drop out percentagePresence and completeness of the research data

If any errors are observed, the files of all study participants within the specific centre will be checked.

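### Adverse events are recorded only if volunteered or noticed by the research side, so by-arm harms for the intensive arms versus usual treatment can be confounded with opportunity to report

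*Protocol article*

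**What the plan says.** The protocol article's section on adverse event reporting and harms {22} defines an adverse event broadly, as any undesirable experience during the study regardless of cause. It then states how events reach the record: "All adverse events reported spontaneously by the subject or observed by the investigator or the research team will be recorded". No scheduled adverse-event enquiry is given.

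The next sentence of {22} does mention the therapist, but only for distress caused by the study's own questionnaires, interviews and observation task: "as observed by the researcher or therapist or as reported by the parents or children themselves". Under {11c}, "therapists are asked to fill in a treatment evaluation form after each therapy session"; the stated purpose of that form is to monitor adherence. The independent physician's twice-yearly file check, also in {11c}, covers "Serious adverse events (SAEs) and if these are reported to the independent physician" among other items.

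Treatment density differs by arm. For ITT and FITT, "The preparation phase consists of two treatment days", and then: "In the intensive phase, the adolescent has three treatment days per week". FITT adds three family therapy sessions. For usual treatment, "TAU is offered about once a week and without therapist rotation".

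Table 3 gives one measurement schedule (T0, T1–11, T12/14, T13) without distinguishing arms. It includes an 8-item child and parent survey on new partner violence and other stressors. Section {17a} says that nobody is blinded during the intervention.

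**The concern.** When events are recorded only if someone volunteers or notices them, the count depends on how often the participant is in front of someone who might hear of them. Here that opportunity differs by design between the intensive arms and TAU, and the direction changes over time: denser contact in FITT and ITT early, possibly denser contact in TAU later. The definition of an adverse event is very broad, which makes counts more sensitive to this.

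The Discussion raises the possibility that confronting traumatic detail is too burdensome for participants, although the consequence it names is avoidance and dropout. Tolerability against lower-frequency care is still something readers will want to know. If a by-arm table of adverse events is published, a difference between FITT or ITT and TAU, or the absence of one, could arise from reporting opportunity alone. The staff who spend most time with the adolescent have no stated duty to feed that record.

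**Working it through.** The plan gives no figure on this point to reproduce. The check is to sum scheduled contact by arm and then ask who can put an event on record.

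**Inputs from the document**
- Preparation phase, ITT and FITT: 2 days, one 90-minute session each.
- Intensive phase, both arms: 3 days a week in weeks 2 and 3, so 6 days, each with "90-min Exposure60-min bodily oriented therapy90-min EMDR", that is 90 + 60 + 90 = 240 minutes. (Table 1 labels this phase week 2 only. I follow the text, which says weeks 2 and 3 and has six memories treated at one per day.)
- FITT family therapy: 3 × 90 minutes. FITT parent therapy: 3 × 60 minutes a week for 2 weeks.
- TAU: about one session a week. Session length and number of weeks are not stated.

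**Contact days in the first 4 weeks**
- ITT: 2 + 6 = 8.
- FITT: 2 + 6 + 3 = 11 if the three family sessions fall on separate days; 2 + 6 + 1 = 9 if all fall on one day.
- TAU: about 4 adolescent sessions. Parents in TAU also see a separate therapist, which this count leaves out.

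**Adolescent contact time**
- ITT: 2 × 90 + 6 × 240 = 1,620 min = 27.0 h.
- FITT: 1,620 + 3 × 90 = 1,890 min = 31.5 h.
- FITT/ITT = 31.5 / 27.0 = 1.17. Adding 6 h of parent therapy gives 37.5 / 27.0 = 1.39.

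**Against TAU over the first 4 weeks (session length assumed)**

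| TAU session | TAU hours | FITT/TAU | ITT/TAU |
|---|---|---|---|
| 45 min | 3 | 10.5 | 9.0 |
| 60 min | 4 | 7.9 | 6.8 |
| 90 min | 6 | 5.3 | 4.5 |

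**Against TAU over the whole treatment (length and duration assumed)**
- 60-minute sessions: FITT/TAU = 31.5/12 = 2.6 at 12 weeks and 31.5/24 = 1.3 at 24 weeks.
- 90-minute sessions: 31.5/18 = 1.75 at 12 weeks and 31.5/36 = 0.9 at 24 weeks.

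The large imbalance is therefore an early one and applies to TAU only. Over full treatment it may shrink or reverse.

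**Who can put an event on record**
- The observers named in {22} are the investigator and the research team, whose measurement schedule is listed alike for all arms.
- The unequal contact is with therapists. Because {22} lists researcher and therapist separately in its next sentence, research team cannot safely be read to include therapists.
- If remarks made in therapy do reach the record, capture varies with therapy density. If they do not, the staff best placed to notice treatment-related events are outside the record. The text does not say which applies.

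**The case against.** The strongest reply is that no planned result is biased. The statistical sections contain no between-arm analysis of adverse events, and {20b} plans no additional analyses. The named observers follow one schedule for all arms, so unequal therapy contact acts only through remarks that someone passes on. Trauma symptoms and new incidents are measured repeatedly in every arm, the centres offer crisis intervention, and physicians sample files for serious events. Reporting lines and form content are also details that an article commonly omits.

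Much of this stands. There is no formal harms test to be biased, and the shared surveys and file checks limit what could be missed. It does not remove the point: {22} states the capture rule rather than leaving it to another document, symptom scales and the incident survey are not an adverse-event enquiry, and any descriptive table by arm inherits the rule.

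A reader might go further and put a number on the bias. Suppose each contact day reveals an existing event with probability 0.2. The recorded shares in 4 weeks are then 1 − 0.8^11 = 91% in FITT and 1 − 0.8^4 = 59% in TAU, a ratio of 1.55. The documents do not support this. The 0.2 is invented, every event must exist from day 1, therapists are treated as a full route of detection although {22} does not name them, and the measurement contacts common to all arms are counted as zero. Adding 4 common contacts gives 96.5% against 83.2%, a ratio of 1.16; adding 11 gives 99.3% against 96.5%, or 1.03. The result is governed by the assumptions.

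A reader might also infer that the primary FITT–ITT contrast is compromised. At 1.17-fold in adolescent hours, and 11 against 8 days at most, it is not materially so.

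**Conclusion.** The point holds in limited form. The protocol fixes passive capture of adverse events, sets no scheduled enquiry, and does not name treating therapists as reporters of treatment-related events. Therapy contact in the first 4 weeks is about 5 to 10 times greater in FITT than in TAU, and about 4.5 to 9 times greater in ITT than in TAU, for assumed TAU sessions of 45 to 90 minutes. Later contact may favour TAU, whose duration is not stated. By-arm harms for FITT or ITT against TAU can therefore be confounded with opportunity to report. This is a risk and not a demonstrated bias: its size cannot be derived from the document, and it depends on whether events mentioned in therapy reach the record. No efficacy result and no planned test is affected.

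**What to change.** - Add the same short, fixed adverse-event question for child and parent to the existing surveys at T1–11, T12/14 and T13, identical in all arms.
- State in {22} that therapists pass on adverse events they learn of, so that they are recorded. The form already completed after each session could carry this.
- Tabulate events by arm over the same calendar period from randomisation, with solicited and spontaneous reports shown separately.

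The cost is one or two survey items at measurement points that already exist and a sentence or two in {22}; no extra visits or staff are needed. Counts will rise in every arm. Recruitment began in March 2021, so families already enrolled will lack the early item, and the table should say so. The research team must also look at the survey answers as they come in.
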